## Methods/design

### Study design and randomization

This multi-centre study in the Netherlands has an unblinded stepped wedge cluster randomized design [32] with pre- (T0) and post-intervention measures after six months (T1), with a follow up after twelve months (T2). The framework of this trial is superiority, whereby we will compare the outcomes between the control and intervention group, and between baseline and follow up data. Seven departments of five University Medical Centres will participate in the study, four kidney transplantation units, one heart transplantation unit, one liver transplantation unit and one lung transplantation unit. The coordinating centre is Erasmus MC, department Nephrology and Transplantation. This department is responsible for coordinating the study, distributing the questionnaires, training of the NPs and the data analysis. A steering committee is present to contribute ideas and to oversee the process.

Given the nature of the programme and the fact that NPs are trained in delivery of the intervention and communication skills, the NPs delivering the intervention cannot be blinded to the group allocation. Therefore, randomization will be performed at the department level. This will be carried out by an independent professional not involved in the study using sealed opaque envelopes. The envelopes with department names and envelopes with start date will be prepared and shuffled by the researcher. The independent professional then randomly chooses the envelopes. All seven participating departments commence the study with standard care i.e. the control period (see Fig. 1) in September 2020. The timing of transition of departments from control to experimental  period is randomized. The first department will be randomized to commence the experimental period in March 2021. During the experimental period, patients receive standard care plus the ZENN intervention. Patients in the control period are different from the experimental period patients, meaning that they will not cross-over.

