**Fig. 1 Fig1:**
[figure not shown]
Flowchart of the study

In the month prior to the initiation of the experimental period for each department, the NPs will be trained in the delivery of the intervention. At this point in time, there will still be patients in the control period who are yet to complete the follow-up measure. During this month they may receive care in the form of a standard consultation from this NP. Therefore, there is potential for ‘contamination’ of these control period patients in the sense that their NPs will have already received the training associated with the intervention. To limit the risk of contamination, the following strategies will be put in place: standard care protocol will be used in all consultations for control period patients, and the questionnaires will not be administered by the NP but will be sent out by the researcher.

The ZENN intervention will be conducted in the outpatient clinic of each participating department. Due to the COVID-19 pandemic, the possibility of carrying out the intervention through tele-medicine is being examined. For the schematic overview of the inclusion, see Fig. 1. To enhance the validity of the study, the Standard Protocol Items: Recommendations for Interventional Trials (SPIRIT) guidelines [33] will be followed.

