### Training

At the moment of transition to the experimental period, NPs will receive training in communication skills and intervention background by a psychologist ([name]). Both trainers were part of the team who developed the ZENN intervention. The content of the standardized training includes knowledge of the steps in the programme protocol, theoretical knowledge of behaviours change techniques, and practicing these techniques through role-play. NPs learn to activate patients to generate their own solutions rather than focusing on the problems and achieve progression towards personal goals in short space of time. The training consists of two blocks of three hours given on the same day. Due to the COVID-19 pandemic, the possibility of carrying out the training through e-learning and video conferencing is being examined. In addition, there is a booster session once implementation has begun with the aim of discussing cases and optimizing standardization between NPs. The experimental period starts immediately the day after the one-day training has been completed. An extensive description of the training according to the CRe-DEPTH criteria developed by Van Hecke et al. (2020) [38] can be found in Supplement A.

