### Sample size

The sample size calculation is based on a power calculation for the primary outcome i.e. the Skills and Technique acquisition scale of the heiQ at T1. Previous studies have shown effect sizes (Cohen’s *d*) of similar interventions on the Skills and Technique Acquisition scale of 0.17, 0.50, 0.25, 0.50, 0.31 and 0.59 [49–54]. Based on these previous results, we estimate the effect size of the intervention to be 0.38, which is the average effect size observed in the previous studies. Using an ANCOVA model applied at the patient level, with an adjustment for baseline Skills and Technique Acquisition and treatment group (pre- or post-intervention), 82 patients per group are needed to obtain a power of 80% to detect a significant effect of the intervention, at a two-sided significance level of .05. To account for the effects of adjustment for covariates, dropout and missing data, and contamination, we aim to include 100 patients per group, 200 in total. Note that the ANCOVA model assumed in the power analysis differ slightly from the linear mixed model described for the primary analysis below.

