### Strengths and limitations

Some strengths and weaknesses of the study design can be identified. The overall strength of the study is that we give patients in the experimental group the opportunity to participate in an intervention that may meet the needs of patients for holistic and tailored self-management support. Existing interventions have an insufficient tailoring to individual needs [18, 22, 56]; therefore, this intervention has the potential to make an important contribution to the lives of transplant recipients and approaches available to post-transplant professionals.

A strength of the stepped wedge design in this study is that the participating departments will be randomized so that, every department will have the opportunity to participate in the experimental period. With a classical randomization, whereby patients, NPs, or departments would be randomized into the control and the experimental arm, half of the patients would not receive the intervention or half of the NPs would not be trained. Randomization at the patient level is not possible due to the fact that nurses learn communication techniques and it is not possible to switch between these techniques during the control and experimental arm. Moreover, randomization at the NP level would be less preferable. Some departments have only one NP and if they will be randomized into the control arm, a whole department would not be able to participate in the intervention.

A limitation of the stepped wedge design is the risk of contamination of control period patients. Although the stepped wedge design eliminates to a great extent control-period patients being treated by a nurse trained in the intervention, there will be some patients at the end of the control period who are treated by and who undergo follow-up measurement once their NP has been trained. This means that it is possible that the patients at the end of the control period may be ‘contaminated’. We will register which control period patients fall into this ‘contamination phase’. We expect that this will be a small group and not be of influence on the findings.

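### The plan expects few control patients to be followed up after their nurse practitioner is trained, but its own dates contradict this

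*Protocol article*

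**What the plan says.** Study design and randomization fixes two dates: "All seven participating departments commence the study with standard care i.e. the control period (see Fig. 1) in September 2020" and "The first department will be randomized to commence the experimental period in March 2021". The same section sets T1 at six months and T2 at twelve.

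Training time is given in two ways. After Fig. 1: "In the month prior to the initiation of the experimental period for each department, the NPs will be trained". Under Training: "The experimental period starts immediately the day after the one-day training has been completed".

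The risk that controls are seen by a trained NP is acknowledged. The main safeguard, in the paragraph after Fig. 1, is that "standard care protocol will be used in all consultations for control period patients"; the other is that the researcher, not the NP, sends the questionnaires. Strengths and limitations says the design removes most of the problem and that affected controls will be registered, then concludes: "We expect that this will be a small group and not be of influence on the findings". No number is given. The same section rejects randomising patients because, for nurses, "it is not possible to switch between these techniques during the control and experimental arm".

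Sample size puts contamination into one combined allowance: "To account for the effects of adjustment for covariates, dropout and missing data, and contamination, we aim to include 100 patients per group". Data analysis compares contaminated with other controls by a t test at T1 and T2, and adjusts the main model only if that test is significant.

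**The concern.** A control is followed for 6 months to T1 and 12 months to T2. The controls at risk are therefore not only those seen around the training month. They are all those enrolled in the last 6 months before training (for T1) or the last 12 months (for T2), in every department. With a first control window of about 6 months, that is a large part of the control group.

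The main safeguard also sits badly with the plan's own argument. If nurses cannot switch between techniques, a trained NP cannot be relied on to give untrained standard care. If they can, the stated reason against randomising patients weakens. Sending questionnaires from the researcher does not change what care the patient receives.

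At stake is how the contrasts are read. If exposure carries over, T1 compares the intervention with a mixture of standard care and care from a trained NP, which shrinks the effect. At T2 the mixture is heavier. Sustained effect is one of the stated aims, so a null T2 contrast could be taken as loss of effect when the controls had been exposed. The reassurance invites readers to set this aside.

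**Working it through.** **Plan's own figure.** Inputs from Sample size: d = 0.38, two-sided 0.05, 80% power, ANCOVA, 82 per group. The T0-T1 correlation r is not stated. With n = 2(1.96 + 0.842)²(1 − r²)/d² and r = 0.5 (assumption): 2 × 7.85 × 0.75 / 0.1444 = 81.5, so 82. The stated figure is reproduced.

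**First department.** Count September 2020 as month 0 and the switch as month 6.
- With a control window of c months, the share with T1 at or after training is min(1, 6/c) under even accrual. For c = 6 it is 6/6 = 100%.
- If training falls in the month before the switch, 100% holds throughout March.
- If training is the day before a switch at the end of March, c is 7 and the share is 6/7 = 86%.
- Only a control enrolled in September 2020 can reach T1 before a training held in March.
- The earliest possible T2 is September 2021, about six months after the switch, so 100% at T2.

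**All seven departments, constant recruitment up to the switch, training at the switch.** Later switch dates are assumed. Share = Σ min(6, c) / Σ c at T1, with 12 in place of 6 at T2.

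| Assumed switches | T1 | T2 |
|---|---|---|
| 1-month steps (c = 6 to 12) | 42/63 = 67% | 63/63 = 100% |
| 1.5-month steps (6 to 15) | 57% | 94% |
| 2-month steps (6 to 18) | 42/84 = 50% | 72/84 = 86% |
| 2.5-month steps (6 to 21) | 44% | 78% |
| Other six all at month 21 | 42/132 = 32% | 78/132 = 59% |

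Training a month earlier raises the T1 range to 36-76%.

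**Less unfavourable assumptions.**
- Each department recruits all its controls, in equal numbers, in its first 3 months. Department T1 shares with 1-month steps are 1, 0.67, 0.33, 0, 0, 0, 0 (mean 29%); with 2-month steps 1, 0.33, 0, 0, 0, 0, 0 (mean 19%). T2 is 100% and 62%. Stretching the steps to 2.5 months gives (1 + 0.17)/7 = 17% at T1 and (3 + 0.5)/7 = 50% at T2.
- Constant recruitment, but at least 2 months under a trained NP required before T1: min(6, c) becomes 4, giving 28/63 = 44% (1-month steps) down to 28/126 = 22% (other six all at month 20).

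**Possible influence.** If exposed controls gain a fraction f of the effect, diluted d = 0.38 × (1 − share × f). Power with 100 analysed per group is Φ(d/√(0.75 × 2/100) − 1.96), with r = 0.5.

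| Share at T1 | f = 0 | f = 0.25 | f = 0.5 |
|---|---|---|---|
| 1/3 | 0.38, 87% | 0.35, 81% | 0.32, 73% |
| 1/2 | 0.38, 87% | 0.33, 77% | 0.29, 64% |
| 2/3 | 0.38, 87% | 0.32, 73% | 0.25, 54% |

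At a share of 19% and f = 0.5, d = 0.344 and n = 100 per group, which uses the whole step from 82 to 100 and leaves nothing for dropout or missing data.

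**The conditional adjustment.** With 100 controls split 50/50 and a true difference of half the effect (0.19 SD), the t test has z = 0.19/√(2/50) = 0.95 and power of about 16%. A non-significant result would say little.

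**The case against.** The visible text fixes only one switch date; Fig. 1, which holds the schedule, is not shown. A reader might infer that the dates alone put a third to two thirds of all controls after training. They do not. That range needs assumed dates for six departments and recruitment continuing to each switch. Early recruitment is plausible: patients qualify from 2 to 13 months after transplantation, so a stock of eligible recipients exists on the first day, and 100 controls over seven departments is about 14 each. This stands, and the overall share must be labelled as conditional.

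A reader might also infer that every first-department control is affected whatever the accrual. That fails if training is the day before a late-March switch: the share is then 86% under even accrual, and lower if recruitment is concentrated in September.

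The plan's affected group is those both treated and measured after training. A T1 date after training is wider, since a control might have no further consultation. The shares are therefore upper bounds.

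Dates cannot show influence. ZENN is a structured programme (Self-Management Web, SMART goal, follow-up sessions) that controls are not meant to receive, and the documents give no basis for any carry-over fraction. Reading the trial as shown to be underpowered goes too far. Dilution would also bias a superiority trial towards no effect, not create a false positive.

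Finally, the plan discloses the risk, registers the patients, names contamination in the sample size and tests for it. That is fair credit. It does not correct the statement that the group will be small, and adjustment waits on a test with little power.

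**Conclusion.** The point holds in limited form. The expectation of a small group is contradicted by the plan's dates: for the first department almost directly (86-100% at T1 under even accrual, 100% at T2), and overall under every schedule worked through. At T1 the overall share is 32-67% under constant recruitment with training at the switch, 19-29% with recruitment in the first 3 months and steps of 1 to 2 months (17% at 2.5 months), and 22-44% if two months under a trained NP are required. At T2 it is half or more of controls in each schedule. All are upper bounds on actual exposure and rest on assumed later switch dates.

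The expectation of no influence is unsupported rather than disproved. It rests on a safeguard that another statement in the plan says cannot work, and its truth depends on an unknown carry-over. With none there is no loss. With an assumed half, d falls to about 0.32-0.25 and power to about 73-54% for shares of one third to two thirds, with 100 analysed per group and r = 0.5. The statement is wrong as written, and correcting it changes how a null T1 or T2 result may be read.

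**What to change.** 1. Strengths and limitations: remove the expectation of a small group without influence and the claim that the design largely removes the problem. Give instead the expected number of controls whose T1 and T2 fall after NP training, computed from the randomised start dates.
2. Sample size: state an assumed dilution from contamination, as a range that includes zero, and the power it leaves.
3. Data analysis: always report a supportive estimate that uses the time from NP training to each control visit, whatever the t test shows. State that a null T2 contrast may reflect exposed controls and does not by itself show loss of effect.
4. Reconcile the safeguard after Fig. 1 with the statement that nurses cannot switch techniques, and the two training times (the month before the switch, or the day before it).

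Cost: wording, and one analysis from dates the trial already holds. The stated power becomes less favourable and the T2 conclusion more guarded. No extra patients are needed.

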## Trial status

Start of inclusion; September 2020, expected end of inclusion May 2022.

## Data Availability

Not applicable, no datasets are included in this study protocol.

## Appendix

**Table 1 Tab1:** Overview of research questions and measures at different time-points—patients

Research questions	Instrument	T0	T1	T2
**Patients in the control period**				
− What are the differences in patients’ self-management skills between control and experimental period	heiQ	X	X	X
− What are the differences in patients’ self-regulation skills in the context of transplantation?	Newly developed self-report instrument	X	X	X
− What is the difference in patients’ medication adherence between the control and experimental period?	BAASIS	X	X	X
− What is the differences in quality of life between patients in the control and experimental period?	WHOQoL-BREF heiQ	X	X	X
− What is the difference in patients’ experience and appreciation of nurse-led care?	Newly developed questions CAHPS		X	
**Patients in the experimental period**				
− What are the differences in patients’ self-management skills between the control and experimental period? − What are the differences in patients’ self-management skills between pre- and post-intervention?	heiQ	X	X	X
− What are the differences in patients’ self-regulation skills in the context of transplantation?	Newly developed self-report instrument	X	X	X
− What is the difference in patients’ medication adherence between patients in the control and experimental period? − What is the difference in patients’ medication adherence between the control and experimental period?	BAASIS	X	X	X
− What is the differences in quality of life after the transplantation between patients in the control and experimental period?	WHOQoL-BREF heiQ	X	X	X
− What is the difference in patients’ experience and appreciation of nurse-led care between the control and experimental period?	Newly developed questions CAHPS		X	
− What is patients’ experience and appreciation of the self-management intervention?	Newly developed questions		X	

**Table 2 Tab2:** Overview of research questions and measures at different time-points—nurse practitioners

Research question	Instrument	T0	T1
− What are the differences in nurses’ self-management support skills between the control and experimental period?	SEPSS-36	X	X
− What are nurses’ experience and appreciation of the self-management intervention?	Semi-structured interview		X
− What is the difference in nurses’ needs-thwarting and needs supporting between the control and experimental period?	COUNSEL-CCE	X	X

## Abbreviations

BAASIS: Basel Assessment of Adherence to Immunosuppressive Medication Scale
COUNSEL-CCE: Coding and Observing Need-Supportive Counselling in Chronic Care Encounters
CAHPS: American Consumer Assessment of Health Plan Survey
heiQ: Health Education and Impact Questionnaire
NP: Nurse Practitioner
NURSE-CC: Nursing Research into Self-Management and Empowerment in Chronic Care
SEPPS-36: Self-Efficacy and Performance in Self-Management Support
WHOQoL-BREF: World Health Organization Quality of Life – Brief Version
ZENN: Zelfmanagement Na Niertransplantatie *Dutch acronym for* Self-Management after Kidney Transplantation
